### Gut Microbiota Analysis

Gut microbiota profiling will be performed using 16S rRNA gene sequencing targeting the V3-V4 region. DNA will be extracted using the Maxwell RSC system (Promega), and library preparation will follow Illumina’s 16S Metagenomic Sequencing protocol [32]. Amplicons will be barcoded, pooled equimolarly, and sequenced on the Illumina MiSeq platform (2×250 bp). Raw reads will be demultiplexed, quality-filtered, and denoised using DADA2 in QIIME 2 to generate amplicon sequence variants and remove chimeras [33,34]. Taxonomic classification will be assigned using a pretrained SILVA 138 database classifier [33]. Microbial diversity will be evaluated using α diversity indexes (Shannon, Faith phylogenetic diversity) and beta diversity metrics (Bray-Curtis, UniFrac distances) [35-38]. Differential abundance analysis will be conducted using appropriate statistical frameworks, such as ANCOM-BC or MaAsLin2, with false discovery rate correction [39]. Downstream analyses will be guided by metadata and study endpoints to identify microbial shifts associated with each intervention.

### Statistical Analysis

Clinical data will be presented as mean (SD) unless stated otherwise. Statistical analyses will be performed using SPSS Statistics (version 28.0; IBM Corp) [40]. The normality of continuous variables will be assessed using the Shapiro-Wilk test. Participants’ baseline characteristics will be summarized using descriptive statistics. Differences in glycemic responses across the 3 study arms will be assessed using either 1-way ANOVA or the Kruskal-Wallis test, depending on data distribution. Changes in clinical variables before and after the intervention will be analyzed using repeated-measures ANOVA, with time (before vs after), group (intervention arm), and the time-by-group interaction as factors. Sociodemographic characteristics, dietary intake, and physical activity levels will be considered as covariates where appropriate. A *P* value of <.05 will be considered statistically significant. Analyses will be conducted according to the intention-to-treat principle, with per-protocol analyses performed for participants who complete the study without major deviations. Missing data will be handled using appropriate imputation methods, and any exploratory analyses will be clearly identified and interpreted with caution.

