### Sample Size

The sample size for this crossover trial was estimated based on detecting a medium effect size (Cohen *f*=0.25), consistent with findings from a recent meta-analysis of soluble fiber supplementation in T2DM, which reported moderate standardized mean differences for HOMA-IR (standardized mean difference −0.58, 95% CI −0.86 to −0.29) [23]. Using G*Power 3.1.9.6, we computed the required sample size for a within-subject repeated-measures ANOVA with 3 conditions (sucralose, saccharin, and placebo), assuming α=.05, and statistical power at 80%, and a moderate correlation (*r*= 0.5) among repeated measurements [24]. The analysis indicated that a minimum of 28 participants would be required. To account for potential dropout or noncompliance, we will recruit 33 participants.

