**Questionnaire**								
	Sociodemographic and medical history	✓						
	Medication record	✓	✓		✓		✓	
	Dietary record	✓	✓	✓	✓	✓	✓	✓
	Physical activity record	✓	✓	✓	✓	✓	✓	✓
	Test product compliance record			✓		✓		✓
	Adverse effect reports			✓		✓		✓

Anthropometric measurements will be obtained using standardized procedures. Body weight will be measured using a calibrated digital scale with participants wearing light clothing, while height will be measured using a stadiometer, ensuring an upright posture and proper head alignment. The average of 2 readings will be recorded for both weight and height, and BMI will be calculated as weight in kilograms divided by height in meters squared (kg/m²). Waist circumference will be measured at the midpoint between the lowest rib and the iliac crest using a nonstretchable measuring tape [25]. Body composition, including body fat and muscle mass, will be assessed using bioelectrical impedance analysis following standard premeasurement guidelines [26]. Blood pressure will be measured twice after a 5-minute rest using an automated sphygmomanometer, and the mean of both readings will be recorded.

For biological specimens, blood samples of approximately 15 mL will be collected from participants at each study visit by trained nurses after a 30-minute rest period. Analyses will include fasting glucose, fasting insulin, glycated hemoglobin (HbA_1c_), lipid profile, and kidney function indicators. Insulin resistance will be estimated using the HOMA-IR, derived from fasting glucose and insulin levels [27]. Samples will be transported and processed according to biosafety and quality control procedures to ensure sample integrity for biochemical analysis and future molecular investigations. Stool samples of approximately 1 g will be collected using standardized fecal collection tubes provided to participants. Preintervention samples will be collected a day before each intervention phase, and postintervention samples will be obtained immediately after the final intervention day. Participants will receive detailed written and verbal instructions to ensure correct collection and handling procedures [28].

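### No analysis scale is fixed for HOMA-IR: a Shapiro-Wilk result picks between two independent-groups tests, and the repeated-measures ANOVA of change has no alternative; a prespecified log-scale within-participant analysis would be better

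*Protocol article*

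**What the plan says.** Under Outcomes, the protocol article makes the change in HOMA-IR the primary outcome. Data Collection repeats the construction: "Insulin resistance will be estimated using the HOMA-IR, derived from fasting glucose and insulin levels".

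The Statistical Analysis section contains four statements that bear on the scale and the test:

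- Presentation: "Clinical data will be presented as mean (SD) unless stated otherwise".
- Distribution check: "The normality of continuous variables will be assessed using the Shapiro-Wilk test". It does not say whether this means values at a visit, changes or model residuals.
- Comparison of glycemic responses across the three arms: 1-way ANOVA or Kruskal-Wallis, chosen by the distribution.
- Before/after change: repeated-measures ANOVA with time, arm and their interaction. No alternative is given for non-normal data.

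No transformation and no ratio-scale estimate is mentioned. The Sample Size section assumes a "within-subject repeated-measures ANOVA with 3 conditions" and "a moderate correlation (*r*= 0.5) among repeated measurements".

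**The concern.** HOMA-IR multiplies two positive concentrations, so spread between men and noise within a man tend to act proportionally. As an illustration, a 20% rise is 0.4 units for a man at 2 and 2.0 units for a man at 10. On the raw scale the second man's changes, real and random, are five times as large, and an unweighted mean change leans on men like him. On the log scale both contribute equally. The effect then reads as a percentage change and splits exactly into a glucose part and an insulin part.

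The stated response to non-normality does not deal with this well. A significance test on the data selects the method, so the primary analysis is not fixed in advance. The fallback it selects is an independent-groups test, although the crossover was chosen so that each man is his own control. The repeated-measures ANOVA, which is the family the sample size rests on, has no fallback. At stake are power and a fixed primary analysis, not the false-positive rate.

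**Working it through.** **1. The plan's own figure.** Inputs from Sample Size: f = 0.25, three conditions, r = 0.5, α = 0.05, power 80%. Noncentrality λ = f² × N × 3 / (1 − r), with 2 and 2(N − 1) degrees of freedom. At N = 28, λ = 0.0625 × 28 × 3 / 0.5 = 10.5. Power is 79.6% at N = 27, 81.3% at N = 28 and 87.8% at N = 33, so the stated minimum of 28 reproduces.

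**2. Assumptions for the scale question.** The documents give no SD or CV for HOMA-IR. The following is therefore assumed: log-normal HOMA-IR, a proportional product effect, and an effect sized so that the log-scale analysis has about 80% power. With every man measured in every arm, the time-by-arm F test equals a repeated-measures F test on the change scores. Two set-ups were simulated.

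- *Set-up A*: between-person SD of log HOMA-IR 0.4 to 0.7, visit noise SD 0.2 to 0.3, one active product, change scores.
- *Set-up B*: total log-SD 0.3 to 0.8 with r = 0.5 or 0.8, both sweeteners equally active, change scores and post-treatment values.

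The SD is defined differently in the two. In B, a total of 0.7 at r = 0.5 is a between-person SD of 0.7 × √0.5 = 0.49. This is one reason why A gives the larger losses at the same nominal SD.

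**3. Set-up A, change scores, log-scale power 80%.** For n = 28 to 33, raw-scale power is 77–80% at SD 0.4 (loss 0–3 points), 73–76% at 0.5 (loss 4–7), 69–73% at 0.6 (loss 7–11) and 65–67% at 0.7 (loss 13–15). A separate run at n = 28 gave about 80% at 0.3, 73–75% at 0.5 and 63–64% at 0.7. In that run Kruskal-Wallis on changes had about 76–79% at 0.5 and 73–74% at 0.7, so it recovered part of the loss.

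**4. Set-up B, change scores, N = 28 (power, %).** The two-stage column applies the stated switch: Kruskal-Wallis if Shapiro-Wilk rejects in any arm, otherwise 1-way ANOVA.

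| log-SD | r | log RM-ANOVA | raw RM-ANOVA | log minus raw | two-stage | Shapiro-Wilk rejects changes in one arm |
|---|---|---|---|---|---|---|
| 0.3 | 0.5 | 82.7 | 83.3 | −0.6 | 84.7 | 12 |
| 0.3 | 0.8 | 80.2 | 79.5 | 0.7 | 80.5 | 15 |
| 0.5 | 0.5 | 81.3 | 80.0 | 1.3 | 83.4 | 30 |
| 0.5 | 0.8 | 82.0 | 76.5 | 5.5 | 81.6 | 29 |
| 0.7 | 0.5 | 81.4 | 72.5 | 8.9 | 84.1 | 53 |
| 0.7 | 0.8 | 81.6 | 68.5 | 13.1 | 79.6 | 57 |

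Here the switch recovers nearly all of the loss or more. At N = 33, raw-scale power on changes is 77–88%, against 87–88% on the log scale.

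**5. Set-up B, post-treatment values, N = 28, r = 0.5 (%).**

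| log-SD | log RM-ANOVA | raw RM-ANOVA | Kruskal-Wallis | Shapiro-Wilk rejects raw values | error SS from the top three men, raw (log) |
|---|---|---|---|---|---|
| 0.3 | 81.1 | 77.6 | 42.9 | 37 | 22 (12) |
| 0.5 | 81.2 | 71.0 | 41.2 | 67 | 32 (12) |
| 0.7 | 81.3 | 62.7 | 41.9 | 90 | 43 (13) |

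The low Kruskal-Wallis power comes from the ignored pairing. An unpaired test of post values works against σb² + σw² (between-person plus visit variance), a change score against 2σw². With σw = 0.3 these are 0.18 and 0.18 at σb = 0.3, but 0.34 and 0.18 at σb = 0.5. The unpaired test therefore falls behind as between-person spread grows.

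**6. Type I error.** Raw-scale repeated-measures ANOVA stays at 3.6–5.1% across all runs.

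**The case against.** The strongest reply is that the article nowhere says HOMA-IR is analysed untransformed, or that Shapiro-Wilk is applied to raw visit values. A reader might infer both, but they come from silence. A check on changes fits the text equally well, the mean (SD) rule allows exceptions, and an article may leave transformation to an analysis plan that is not shown. This stands, and the point is not that the plan forbids a log scale. What the article does state is its response to non-normality: a test-driven switch for one comparison and no alternative for the other.

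A reader might also infer that a few men will dominate the primary test whatever happens. The text does not support that. The rank test limits extreme values when it is triggered, and on change scores it recovers part or all of the loss. The article also does not say whether the arm comparison or the repeated-measures ANOVA carries the primary outcome, or whether glycemic responses are changes or post values.

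The size is conditional too. Log-normal data and a proportional effect favour the log scale by construction. Entry is broad in HbA1c and disease duration, but limited to men aged 30 to 59 with BMI 23.0 to 29.9 on oral treatment only, so the high-spread settings may not arise. That argues for quoting a range. It does not argue for leaving the choice to a normality test.

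**Conclusion.** The concern holds in a limited form. The plan fixes no scale for its primary outcome, lets a normality test choose between two independent-groups tests, and leaves the repeated-measures ANOVA without an alternative. If HOMA-IR is analysed raw, the loss on change scores ranges from negligible at low spread to about 9 to 16 points at a log-SD of 0.7. Planned power at N = 28 is only 81.3%, so even a loss of 2 points takes it below 80%; at N = 33 it starts from 87.8%.

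This is a matter of efficiency and prespecification. A reader might conclude that the primary test is invalid or that false positives are inflated; the simulations show neither. Nor do the documents show that the trial is underpowered, because they give no SD for HOMA-IR and the ranges rest on assumed spread, log-normality and a proportional effect.

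**What to change.** In Statistical Analysis, state that HOMA-IR and fasting insulin are log-transformed before analysis whatever the Shapiro-Wilk result, and that log HOMA-IR is analysed in a within-participant crossover model. Report the product effect as a ratio of geometric means with 95% CI, and describe HOMA-IR by geometric mean or median (IQR). Check model residuals instead of using a normality test to switch methods, and keep the raw scale as a sensitivity analysis. The log transformation alone does not restore the pairing that 1-way ANOVA and Kruskal-Wallis ignore, so both parts of the change are needed.

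The cost is one or two sentences, with no new data, and no participant had been enrolled as of December 2025. The small downside is that the primary estimate becomes a ratio instead of a mean difference. Sample Size should therefore note that its standardized mean difference of −0.58 refers to a different scale.

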## Methods

### Study Design

This study is a double-blind, randomized, placebo-controlled crossover trial. The crossover design allows each participant to serve as their own control across 3 intervention phases. Each participant will complete a 12-week protocol comprising a 1-week run-in period followed by 3 intervention phases, each separated by a 4-week washout period. A total of 6 study visits, comprising 3 preintervention and 3 postintervention assessments, will capture baseline and postintervention data. During the run-in and washout periods, participants will maintain their habitual diet and physical activity. The study will be conducted at a government primary care facility situated in an urban area. Recruitment will be facilitated through clinic listings and physician referrals. Written informed consent will be obtained after participants receive detailed verbal and written explanations of the study procedures, risks, and rights. The study timeline is summarized in Figure 1.

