### Outcomes

The primary outcome is the change in insulin sensitivity, assessed using the homeostatic model assessment for insulin resistance (HOMA-IR), derived from fasting glucose and insulin concentrations. The secondary outcome is the change in gut microbiota composition and diversity, analyzed through 16S rRNA gene sequencing. Alpha and beta diversity indexes will be calculated to evaluate within- and between-sample diversity, and differential abundance analysis will be performed to identify microbial taxa associated with each intervention.

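### The across-arm comparison names independent-groups tests (1-way ANOVA, Kruskal-Wallis) for a crossover sized on a within-participant test; how much power this costs depends on a correlation the plan does not give

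*Protocol article*

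**What the plan says.** Study Design describes a three-period crossover: "The crossover design allows each participant to serve as their own control across 3 intervention phases". The Discussion gives the reduction of between-person variability as a reason for this choice.

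Outcomes defines the endpoint as a change: "The primary outcome is the change in insulin sensitivity, assessed using the homeostatic model assessment for insulin resistance (HOMA-IR"). Table 1 schedules blood sampling before and after each phase, so six HOMA-IR values per participant are expected.

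Sample Size is built on the pairing: "we computed the required sample size for a within-subject repeated-measures ANOVA with 3 conditions", with Cohen f=0.25, α=.05, 80% power and a correlation of 0.5 among repeated measurements. It arrives at 28 participants, with 33 to be recruited.

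Statistical Analysis then names two analyses. Glycemic responses across the arms "will be assessed using either 1-way ANOVA or the Kruskal-Wallis test, depending on data distribution". Before-after changes in clinical variables go to a repeated-measures ANOVA "with time (before vs after), group (intervention arm), and the time-by-group interaction as factors". The section does not say which of the two decides HOMA-IR.

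**The concern.** 1-way ANOVA and Kruskal-Wallis assume three independent samples. In this trial the three samples are the same people. If a participant's values are positively correlated across arms, between-person variance stays in the error term although it plays no part in the differences between arms. The test then rejects too rarely, both when there is no effect and when there is one.

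The name 1-way ANOVA could be shorthand for the one-factor repeated-measures version. Its companion makes that unlikely: Kruskal-Wallis is the rank test for independent groups, and the paired rank test would be Friedman. The Shapiro-Wilk switch therefore chooses between two tests that both ignore the pairing.

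At stake is whether the comparison that answers the trial's question has the power claimed for it. Since the results are meant to inform views on sweetener safety, a missed effect is the direction that matters.

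**Working it through.** **Inputs.** From Sample Size: f=0.25, m=3 conditions, r=0.5, α=0.05, N=28 (33 recruited). Assumed here: normal data, equal correlations between arms (sphericity) and equally spaced arm means.

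**1. The plan's own figure.** For the within-participant test, λ = f²·N·m/(1−r), with m−1 and (N−1)(m−1) degrees of freedom.
- N=28: λ = 0.0625×28×3/0.5 = 10.5, df 2 and 54, power 0.812.
- N=27: λ = 10.125, power 0.796.
- N=33: λ = 12.375, power 0.878.

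The smallest N reaching 80% is 28, as stated. Allowing 15% dropout, 28/0.85 = 32.9, so 33. The figure needs the division by 1−r, that is, a test that uses the pairing.

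**2. The named tests on one value per arm.** With correlation r between arms, the null expectation of the between-arm mean square is (1−r)σ², while the 1-way error mean square stays near σ². At r=0.5 the F ratio is therefore about half what the F table expects. The critical value for df 2 and 81 is 3.11, so the effective threshold is about 3.11/0.5 = 6.2, and an F variable exceeds that about 0.3% of the time. Simulation (20,000 runs; 10,000 for rank tests) at r=0.5 gives:

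| Test | Type I error, n=28 | Power, n=28 | Power, n=33 |
|---|---|---|---|
| Within-participant ANOVA | 5.2% | 81% | 88% |
| 1-way ANOVA | 0.4% | 45% | 56% |
| Kruskal-Wallis | 0.4% | 42% | 53% |
| Friedman | 4.8% | 66% | 75% |

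**3. Dependence on the correlation (n=28).**

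| r between arms | 1-way ANOVA power | Within-participant power | 1-way type I error |
|---|---|---|---|
| 0 | 51% | 50% | 5.0% |
| 0.3 | 47–48% | 66% | 1.5% |
| 0.5 | 45% | 81% | 0.4% |
| 0.7 | 42% | 96% | 0.01% |

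**4. Change scores.** The stated outcome is a change, and the plan gives no correlation between changes in different phases. Suppose r=0.5 holds among all six measurements (an assumption).
- Variance of a change: 2σ²(1−r) = 2σ²×0.5 = σ², so f stays at 0.25.
- Covariance of changes from two phases: (r−r−r+r)σ² = 0.

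The r=0 row then applies: λ = 0.0625×28×3 = 5.25. Simulated directly, 1-way ANOVA has 5.0% type I error and 51% power, and the within-participant test about 5% and 50%. At n=33 the powers are about 58–59% and 58%. Pairing the changes gains nothing here. Under the same assumption, the within-participant test on post-phase values keeps its 81% and 88%.

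**5. The repeated-measures ANOVA.** With two time points and complete data, the time-by-arm interaction is a test on change scores. If arm is entered as a between-person factor, it equals the 1-way ANOVA on changes. If arm is a within-participant factor, it equals the paired test on changes. The text does not say which is meant.

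**The case against.** The strongest reply is that the primary outcome is a change, so the 0.4% and 45% describe a variable the trial may not analyze. This stands. With uncorrelated changes, 1-way ANOVA loses nothing to the paired test, and changing the test alone would not restore 80%. A positive correlation between changes would bring some loss back, but the plan gives no value.

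A second reply is that a repeated-measures ANOVA is already planned, its wording fits the outcome, and nothing says arm is between-person. A reader might infer that the plan ignores pairing altogether; the documents do not support that. They leave two analyses of glycemic outcomes side by side, one unsuited to the design and the other ambiguous about arm.

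A third concerns consequences. A reader might infer that a real sweetener effect would probably be reported as no difference. At the recruited n=33, 1-way ANOVA has 56% power even on single values at r=0.5, so that is not shown; it would also require the repeated-measures result to be ignored. Nor does the trial need the 159 participants (53 per arm) of an independent-groups design, since no such trial is planned.

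The period term, log scale and covariates may properly be left to a full protocol or analysis plan. The named tests are different: they are stated, and they do not fit the design.

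**Conclusion.** The wording is wrong as it stands and should be corrected. The tests named for the arm comparison contradict both the crossover design and the test behind the sample size, and the section does not say which analysis governs HOMA-IR.

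The size of the damage is a range. At n=28 the power lost by choosing 1-way ANOVA over the within-participant test runs from none (uncorrelated changes) to about 36 points (81−45, single values at r=0.5); at r=0.3 it is about 18 to 19 points. Type I error runs correspondingly from about 5% down to 0.4%. A reader might infer that it is always far below 5%, or that the independent-groups test explains every shortfall from 80%. Neither follows: with uncorrelated changes the shortfall to about 50% belongs to the change score. In every case examined the error is conservative, able to hide an effect but not to inflate false positives.

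These figures rest on normality, sphericity, equally spaced means and the plan's own f and r.

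**What to change.** Name one primary analysis of HOMA-IR that keeps the pairing. Either of these would do:

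- a linear mixed model of post-phase HOMA-IR (preferably log-transformed), with arm, period and pre-phase value as fixed effects and participant as a random effect; or
- a repeated-measures ANOVA with arm explicitly declared a within-participant factor.

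Remove 1-way ANOVA, Kruskal-Wallis and the normality-test switch between them. If a rank check is wanted, use Friedman or a within-participant permutation test as a sensitivity analysis.

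State which variable the sample-size r=0.5 refers to. If post-phase values adjusted for the pre-phase value replace the change score, say that this move is part of the power gain and align the Outcomes wording with it. If the change score stays, a paired test on changes alone may still fall short of 80%, and the power statement should say so.

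The cost is wording in the statistical and outcome sections; the data and software (SPSS) are unchanged. The article reports no enrollment as of December 2025, so the change can be made before any outcome data exist.

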### Intervention

Participants will receive 1 of 3 interventions: sucralose, saccharin, or a placebo, for 7 consecutive days during each intervention phase. Participants will consume the assigned capsule each morning after breakfast with plain water to standardize timing and minimize missed doses. Dosages will be adjusted based on body weight according to national guidelines, with 5 mg/kg for sucralose and 2 mg/kg for saccharin [22]. The placebo, consisting of 500 mg of calcium carbonate, will be administered under identical conditions and is considered physiologically inert at this dose [9].

Randomization and allocation concealment will be conducted by external personnel not involved in recruitment, data collection, or analysis. A computer-generated block randomization sequence will assign participants to 1 of 3 intervention orders (sucralose, saccharin, or placebo) to ensure balanced allocation across participants. All test products will be encapsulated in identical opaque capsules and packaged in indistinguishable small plastic pouches. Labeling will be performed by external personnel according to the intervention sequence, where each package will be marked as “first intervention,” “second intervention,” or “third intervention” to maintain blinding. Both participants and investigators will remain blinded throughout the data collection period. The randomization code will be securely stored and accessible only in the event of a medical emergency.

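### The stated crossover ANOVA leaves out phase (period 1/2/3), so a phase effect on the 7-day HOMA-IR change would inflate the error and, with uneven completers, bias the sweetener-placebo contrast

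*Protocol article*

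**What the plan says.** The Study Design section describes a 12-week schedule: a "1-week run-in period followed by 3 intervention phases, each separated by a 4-week washout period". Its rationale is that "The crossover design allows each participant to serve as their own control across 3 intervention phases". Under Intervention, a block randomization assigns each man to "1 of 3 intervention orders (sucralose, saccharin, or placebo) to ensure balanced allocation across participants". The orders themselves are not listed.

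The Statistical Analysis section gives two comparisons. First, "Differences in glycemic responses across the 3 study arms will be assessed using either 1-way ANOVA or the Kruskal-Wallis test", depending on the data distribution; which response this refers to (change or post value) is not stated. Second, changes in clinical variables go into a repeated-measures ANOVA "with time (before vs after), group (intervention arm), and the time-by-group interaction as factors". The only further terms are these: "Sociodemographic characteristics, dietary intake, and physical activity levels will be considered as covariates where appropriate". Neither comparison contains the phase or the order. The primary outcome (Outcomes section) is the change in HOMA-IR, and Table 1 shows blood taken before and after each phase.

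**The concern.** In a three-period crossover, phase is a design factor known for every sample. The article defines time as before versus after, so that term cannot stand in for phase 1, 2 or 3. Two features of the plan might seem to cover the gap, but neither does. The 4-week washout (Discussion) is aimed at carryover, which is not the same as a phase effect. Balanced allocation holds at entry only: the plan recruits 33 to end with at least 28, allows withdrawal for several reasons, and includes per-protocol analyses.

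A phase effect on the 7-day change is conceivable. For example, first exposure to food and activity recording could alter behaviour more in phase 1 than later. If such an effect exists, the model as written treats it as noise. That lowers power in a trial asking whether sweeteners do harm, where a missed effect could be read as reassurance. If the three orders end with unequal numbers, part of the effect also moves into the arm contrast.

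**Working it through.** **Inputs.** From the Sample Size section: f = 0.25, 3 within-participant conditions, alpha 0.05, r = 0.5, target power 80%, minimum 28, recruited 33. Assumed, because the documents do not give them: orders forming a cyclic Latin square (ABC, BCA, CAB); a linear drift of d SD per phase in the analysed variable, with d from 0 to 0.5; total SD 1; equally spaced arm means.

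**1. The plan's own figure.** λ = f²·n·m/(1−r) = 0.0625 × 28 × 3 / 0.5 = 10.5, with 2 and 54 degrees of freedom. Power is 81.25% at n = 28 and 79.6% at n = 27, so the stated minimum of 28 is reproduced. Equally spaced means with range R have f = R/√6, so the planned extreme-arm difference is 0.25 × √6 = 0.61 SD.

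**2. Which drift matters.** A shift common to a phase's pre and post values drops out of post minus pre. Simulation (4,000 runs per case, no true arm effect, 0.3 SD per phase) shows the following:
- Level drift, time-by-group test: error mean square 0.50, rejection 5.2% at 11/11/11, bias within 0.007 SD at every split tried. It is unaffected.
- Level drift, post values compared: rejection 1.9% at 11/11/11, bias 0.055 SD at 11/9/8.
- Drift in the 7-day change, time-by-group test: error mean square 0.59, rejection 2.6% at 11/11/11, bias 0.057 SD at 11/9/8.

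**3. Error and power when orders are balanced.** With phase omitted, the expected error mean square is (1−r) + d²·n/(n−1). At n = 33 and d = 0.5 this is 0.5 + 0.25 × 33/32 = 0.76. Simulation (8,000 runs per case) gives:

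| d per phase | Error MS (11/11/11) | Null rejection, no period (11/11/11) | Power n=28 (10/9/9), no period | Power n=28, with period |
|---|---|---|---|---|
| 0 | 0.50 | 5.0% | 81.4% | 81.0% |
| 0.1 | 0.51 | 4.5% | 82.2% | 81.7% |
| 0.2 | 0.54 | 3.7% | 80.0% | 80.6% |
| 0.3 | 0.59 | 2.6% | 78.6% | 81.7% |
| 0.4 | 0.66 | 1.7% | 74.3% | 81.0% |
| 0.5 | 0.76 | 1.2% | 68.8% | 81.1% |

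The simulated power without period is somewhat favourable. A 10/9/9 split is not exactly balanced, and here the small bias runs with the assumed effect (2/28 × 0.5 = 0.036 SD at d = 0.5). Putting the inflated error straight into the noncentral F, with λ = 10.5/1.083, 10.5/1.187 and 10.5/1.519, gives 77.9%, 73.8% and 62.4% at d = 0.2, 0.3 and 0.5.

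**4. Bias when completers are uneven.** For orders ABC, BCA, CAB with n1, n2, n3 completers, the mean phase position of C minus that of A is (2·n1 − n2 − n3)/n. The bias is d times this.
- 11/9/8: 5/28 × d = 0.036 (d = 0.2) or 0.071 (d = 0.4).
- 11/10/7: 5/28 × d = 0.045 (d = 0.25) or 0.089 (d = 0.5).
- 6/11/11, all five losses in one order: 10/28 × d = 0.071 (d = 0.2) or 0.143 (d = 0.4) in size. At d = 0.5 the same formula gives 0.18, the extreme corner.
- 11/11/11: zero.

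Simulation of the 11/9/8 and 6/11/11 splits agrees with the formula. Against 0.61 SD, 0.036 to 0.143 is about 6% to 23%. These are the C minus A values. Whether that pair is sweetener-placebo or sweetener-sweetener depends on which order loses participants. With period in the model, the bias is about 0 throughout.

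**5. Cost of the term.** Error degrees of freedom go from 54 to 52. Power at n = 28 goes from 81.25% to 81.16%, and at n = 27 it is 79.5%, so the minimum stays 28.

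**The case against.** The strongest reply is that the quoted test is built on pre-post changes with a fresh baseline in every phase, so most of what one calls drift (assay level, general participation effects) cancels. That stands. A reader might infer that any drift across the 12 weeks damages the primary test; step 2 shows it does not.

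Second, no drift size is documented, and 0.5 SD per phase means 1.0 SD from phase 1 to phase 3, more than the planned effect of 0.61 SD. Participants are selected as clinically stable and asked to keep their habitual diet. This also stands: the upper end is a stress case.

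Third, with balanced orders the test becomes conservative, so omission creates no false positives there. In the uneven null scenarios simulated without period, the overall test rejected between 2.6% and 5.2% of the time, so an inflated type I error is not supported either.

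Fourth, the bias figures are for completers, whereas the plan is intention-to-treat with an unspecified imputation method. What imputation would do to balance over orders is not known.

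Fifth, this is a condensed article, and its factor list does not name participant either, so it may not be literally complete. That softens the criticism but does not remove it. The article chose to write out the factors and covariates, and phase is not among them.

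**Conclusion.** The point holds in a limited form. The model as written omits a known design factor of the crossover. The omission matters for the primary test only if the 7-day HOMA-IR change differs by phase, or if post values are what is compared. Under the stated assumptions, the loss at 0.2 to 0.3 SD per phase is roughly 1 to 3 points of power in simulation, or about 3 to 7 by the direct approximation. It becomes substantial only at the upper end of the range. Bias arises only when such drift meets uneven completion over orders, and is then about 0.04 to 0.14 SD for drifts of 0.2 to 0.4.

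All of this rests on an assumed drift and an assumed cyclic set of orders. If the three orders are not a Latin square, phase is partly confounded with arm even without dropout. The documents do not support reading this as an error in the sample size, which is reproduced. It is worth correcting because the remedy costs almost nothing and, according to the Results section, no participant had been enrolled as of December 2025.

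**What to change.** In the Statistical Analysis section, replace the factor list for the primary outcome with a within-participant model for the HOMA-IR change: treatment and period (phase 1, 2, 3) as fixed effects, participant as a random effect. Take the sweetener-minus-placebo contrasts from that model. State which response the 1-way ANOVA or Kruskal-Wallis comparison uses, or drop it in favour of this model. List the three orders. A sequence term is optional; no benefit from it was shown.

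The cost is a change of wording and two error degrees of freedom. No further data are needed, since the visit schedule already identifies the phase of every sample. The wording should be fixed before unblinding, so that the term cannot look data-driven.
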